### **9.9. Planned subgroup analyses**

Interpretation of subgroup analysis will be treated with caution (output will be treated as exploratory rather than definitive). Analysis will be limited to the primary outcome only, and the following subgroups based on Background Treatment Regimen at Randomisation:

- No background immunosuppressive therapy; long term maintenance prednisolone therapy; long term maintenance prednisolone therapy plus other immunosuppressive therapies; other immunosuppressive therapies alone.
- On prednisolone vs. not on prednisolone
- On other immunosuppressant vs. not on other immunosuppressant

The effects of these subgroups will be examined by including a treatment group by subgroup interaction parameter in the final binomial model.

### **9.10. Sensitivity analyses**

Sensitivity analyses will be limited to the primary outcome and will consist of:

- URTI-related relapse (Worse) / no URTI-related relapse (Best) and no URTI-related relapse (Best) / URTI-related relapse (Worse) for active and placebo groups respectively.

As an additional analysis, the number of URTI and non-URTl related relapses along with the number of participants who had a relapse in the modified ITT cohort will be compared to the number of non-URTl related relapses in that of the excluded cohort. It would be anticipated that those who have been excluded experience fewer relapses on the basis that they did not experience an URTI. However, if the numbers are similar it might be the case that some URTIs went unreported in this excluded population.

|                                                                                                                                                                                                                                                                                                                                                                                                                                                                                                                                                                                                                                                                                                                                                                                                                                                                                                                                                                                                                                                                                                                                                                                                                                                                                                                                                                                                                                                                                                                    |
|--------------------------------------------------------------------------------------------------------------------------------------------------------------------------------------------------------------------------------------------------------------------------------------------------------------------------------------------------------------------------------------------------------------------------------------------------------------------------------------------------------------------------------------------------------------------------------------------------------------------------------------------------------------------------------------------------------------------------------------------------------------------------------------------------------------------------------------------------------------------------------------------------------------------------------------------------------------------------------------------------------------------------------------------------------------------------------------------------------------------------------------------------------------------------------------------------------------------------------------------------------------------------------------------------------------------------------------------------------------------------------------------------------------------------------------------------------------------------------------------------------------------|
| 10. Analysis of sub-randomisations                                                                                                                                                                                                                                                                                                                                                                                                                                                                                                                                                                                                                                                                                                                                                                                                                                                                                                                                                                                                                                                                                                                                                                                                                                                                                                                                                                                                                                                                          |
| Not Applicable.                                                                                                                                                                                                                                                                                                                                                                                                                                                                                                                                                                                                                                                                                                                                                                                                                                                                                                                                                                                                                                                                                                                                                                                                                                                                                                                                                                                                                                                                                                    |
| 11. Health economic analysis                                                                                                                                                                                                                                                                                                                                                                                                                                                                                                                                                                                                                                                                                                                                                                                                                                                                                                                                                                                                                                                                                                                                                                                                                                                                                                                                                                                                                                                                                |
| As indicated in the protocol there will also be an economic analysis. The details of this analysis are documented separately.                                                                                                                                                                                                                                                                                                                                                                                                                                                                                                                                                                                                                                                                                                                                                                                                                                                                                                                                                                                                                                                                                                                                                                                                                                                                                                                                                                                      |
| 12. Statistical software                                                                                                                                                                                                                                                                                                                                                                                                                                                                                                                                                                                                                                                                                                                                                                                                                                                                                                                                                                                                                                                                                                                                                                                                                                                                                                                                                                                                                                                                                    |
| Statistical analysis will be undertaken in the following statistical software packages: SAS software and Stata.                                                                                                                                                                                                                                                                                                                                                                                                                                                                                                                                                                                                                                                                                                                                                                                                                                                                                                                                                                                                                                                                                                                                                                                                                                                                                                                                                                                                    |

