#### **4.29 Statistical Analysis**

The Statistical Analysis Plan describes the planned analyses for PREDNOS 2 in full detail. A summary of the main analysis methods are described here.

The primary endpoint is the first URTI-related relapse of nephrotic syndrome (URT-related relapse is defined as 3 days of Albustix 3+ proteinuria within 14 days of onset of an URTI) which occurs during the 12 month follow-up period. The proportion of subjects that experience an URTI-related relapse will be calculated for the two study treatment arms, and compared using a chi-squared test. Treatment effects will be expressed as relative risks with 95% confidence intervals.

This was chosen as the primary endpoint as it is hypothesised that giving daily prednisolone at time of URTI will reduce the subsequent development of disease relapse. If this hypothesis is correct, then those subjects randomised to placebo will experience more URTI-related relapses than those subjects randomised to active drug. This would mean that subjects in the placebo arm are more likely to undergo intensification of immunosuppressive therapy. This in turn would reduce the chances of the subjects in the placebo arm from having further relapses (both URTI-related and non URTI-related) which introduces bias. Therefore, all subjects will be followed-up for 12 months to also assess the relapse rates between the two treatment arms over a 12 month period as a secondary endpoint, but due to these potential biases, the primary endpoint will focus on the first URTI-related relapse. The analysis of the secondary endpoints for relapses per year will assess incidence (relapse) density rates for the two treatment arms and rate differences will be calculated for both URTI and non-URT related relapse of nephrotic syndrome over the 12 month follow-up period. Appropriate regression analysis (e.g. Poisson) will be used to compare relapse rates in the two treatment groups, should there be an imbalance in any important co-variables (e.g. URTI rates across the two study arms).

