The secondary endpoints include both continuous and categorical data items. The dichotomous data (e.g. incidence of escalation of background immunosuppressive therapy) will be analysed as per the primary outcome. Continuous data (e.g. prednisolone dose, quality of life scores) will be expressed as means and standard deviations, with differences in means and 95% confidence intervals. Longitudinal plots of the data over time will be constructed for visual presentation of the data. Data will be analysed using mixed effect repeated measures models with the interventions specified as independent variables. Baseline data will be included in the model as a covariate.

Analyses will be of all randomised subjects using intention to treat, except for those who do not have an URTI following randomisation. Over the course of the study up to the 12th July 2016, the number of patients who have completed the trial without experiencing at least one URTI is approximately 24% which is higher than the originally estimated <10% at the start of the trial. Exclusion of these subjects will result in no bias as these drop-outs are not related to the treatment and should by chance be equally distributed across the two treatment arms (this will be monitored throughout the trial). Sensitivity analyses will be performed on the 12 month data analyses due to the issues raised above. These analyses will be fully outlined in the Statistical Analysis Plan, and will include analyses with subjects censored at point of treatment escalation.

The only subgroup analyses planned are by the background treatment regimen that the subjects are on at randomisation (no long-term treatment; on long term maintenance prednisolone therapy; on other immunosuppressant therapy with long term maintenance prednisolone therapy; on other immunosuppressant therapy without prednisolone); an analysis comparing those subjects on prednisolone versus those not on prednisolone; and an analysis comparing those subjects on other immunosuppressant therapy versus those not on other immunosuppressant therapy. The study is not powered to detect differences in treatment effect across these subgroups, so these analyses will be considered as hypothesis generating.

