## **9.2. Distributional assumptions and outlying responses**

Distributional assumptions (e.g. normality of regression residuals for continuous outcomes) will be assessed visually prior to analysis; although in the first instance the proposed primary method of estimation in this analysis plan will be followed. If responses are considered to be particularly skewed and/or distributional assumptions violated, the impact of this will be examined through sensitivity analysis; this will consist of transformation of responses prior to analysis (e.g. log transformation) in the first instance. If extreme values are apparent and considered to be affecting the integrity of the analysis, a sensitivity analysis consisting of removing the outlying response(s) and repeating the analysis will be performed. Output from these analyses, if performed, will be described and presented alongside the original analysis (or included, e.g. in appendices) with the excluded values clearly labelled.

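### The protocol promises 12-month relapse analyses censored at treatment escalation, but the SAP does not contain them

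*Combined protocol and SAP*

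**What the plan says.** Protocol 4.29 explains why the primary endpoint stops at the first URTI-related relapse. If the hypothesis is right, "subjects in the placebo arm are more likely to undergo intensification of immunosuppressive therapy", which lowers their chance of "having further relapses (both URTI-related and non URTI-related) which introduces bias". Later in the same section it commits to a remedy for the secondary comparisons: "Sensitivity analyses will be performed on the 12 month data analyses due to the issues raised above". It leaves the detail to the SAP: "These analyses will be fully outlined in the Statistical Analysis Plan, and will include analyses with subjects censored at point of treatment escalation".

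Protocol 4.10 allows escalation after two or more relapses within six months, or for unacceptable adverse effects, and keeps escalated children under follow-up.

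SAP 9.10 sets the scope: "Sensitivity analyses will be limited to the primary outcome and will consist of" one pair of best/worst-case scenarios. It then adds a descriptive comparison of relapses in the modified ITT cohort with those in the children who had no URTI. SAP 9.6 estimates incidence rate ratios for URTI-related relapse and for any relapse by Poisson regression, with an offset for time in the trial. It also compares between arms the number of children escalated. Neither section mentions cutting follow-up at escalation.

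**The concern.** The two relapse rates over 12 months are the outcomes most exposed to the mechanism that the protocol describes. Escalation is triggered mainly by relapse and follow-up continues afterwards, so an effective treatment produces less escalation on active drug and more on placebo. The placebo rate then falls for a reason other than the study drug, and the rate ratio moves towards 1.

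The protocol relies on the SAP for the analysis that would address this. The SAP omits it and gives no reason. A reader of the final report would see the full-follow-up rate ratio without the companion analysis that the protocol says will be there.

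**Working it through.** **Side by side.** Protocol 4.29 requires sensitivity analyses of the 12-month data, specified in the SAP and including censoring at escalation. SAP 9.10 restricts sensitivity analyses to the primary outcome. SAP 9.6 uses total time in the trial. SAP 9.3 also confines missing-data sensitivity work to the primary outcome. No other section supplies the analysis.

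**No figure to reproduce.** The documents state no escalation rate by arm and no effect of escalation on relapse. The sample size (250 evaluable, 360 recruited) concerns the primary outcome and is not affected. Everything below is illustration.

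**Simple arithmetic.** Let *e* be the proportion escalated in an arm, *f* the fraction of the year remaining, and *r* the proportional cut in later relapses. Then

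observed ratio = true ratio × (1 − e_active × f × r) / (1 − e_placebo × f × r).

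The true ratio is assumed to be 0.65.

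- Mild case: 30% of placebo and 20% of active children escalated at month 6, later relapses halved. 0.65 × (1 − 0.20 × 0.5 × 0.5) / (1 − 0.30 × 0.5 × 0.5) = 0.65 × 0.950 / 0.925 = 0.668. The shift is 0.018, or 0.018/0.35 = 5% of the effect.
- Strong case: 50% and 25% escalated at month 4, later relapses cut by 80%. 0.65 × (1 − 0.25 × 8/12 × 0.8) / (1 − 0.50 × 8/12 × 0.8) = 0.65 × 0.867 / 0.733 = 0.768. The shift is 0.118, or 0.118/0.35 = 34% of the effect.

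**Simulation.** Recurrent relapses over 12 months, 60,000 children per arm. The placebo rate is 1.8 per year, the control-arm rate that protocol 3.1 reports for the Indian trial. Each child escalates at the second relapse within six months (the relapse rule of protocol 4.10, assumed always acted on), after which the relapse rate is multiplied by 1, 0.5, 0.25 or 0.1 (assumed). Between-child variation is either none or a gamma frailty with variance 0.5 (assumed). Cells show the full-follow-up ratio / the ratio censored at escalation.

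| True ratio, frailty variance | ×1 | ×0.5 | ×0.25 | ×0.1 |
|---|---|---|---|---|
| 0.50, none | 0.498 / 0.499 | 0.540 / 0.500 | 0.563 / 0.497 | 0.585 / 0.505 |
| 0.65, none | 0.651 / 0.651 | 0.684 / 0.647 | 0.711 / 0.653 | 0.724 / 0.648 |
| 0.50, 0.5 | 0.501 / 0.547 | 0.557 / 0.551 | 0.588 / 0.544 | 0.612 / 0.544 |
| 0.65, 0.5 | 0.654 / 0.693 | 0.694 / 0.684 | 0.726 / 0.690 | 0.750 / 0.691 |

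Escalation occurs in 41–47% of placebo and 19–28% of active children. Where escalation lowers later relapses, full follow-up moves the ratio towards 1 by 0.034 (0.684 − 0.65) to 0.112 (0.612 − 0.50). Where it does not (×1), full follow-up is unbiased.

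Censoring recovers the true ratio when children do not differ in underlying relapse rate. With frailty it is off by about 0.03 to 0.05, because children censored early are those prone to relapse.

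**The case against.** The strongest reply is that the plan already limits the damage. The primary endpoint was chosen to avoid this bias. SAP 9.6 compares escalation by arm, so a difference would be visible. It also compares the number of children with any relapse, which is largely protected: a child escalated under the two-relapse rule has normally already counted as an event. SAP 9.10 does look at 12-month relapses in its comparison with the no-URTI children, which answers the other issue raised in protocol 4.29. All of this stands. It narrows the gap to the two rate ratios but does not close it, since none of these analyses shows how far escalation moves them.

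A second reply is that the promised analysis is itself biased. That is also right. In the frailty rows with a halved rate, the censored ratios (0.551 and 0.684) barely improve on full follow-up (0.557 and 0.694). Where escalation has no effect, the censored ratio is the worse of the two. This argues for showing both, not for dropping one without comment.

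A third reply is that the strong arithmetic case is stretched. At 1.8 relapses per year the expected number in four months is 0.6, so the chance of two or more is 1 − e^(−0.6) × (1 + 0.6) = 12%, far below 50%. Earlier escalation is possible if relapses before randomisation or adverse effects count. The strong case is best read as an upper bound.

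**Conclusion.** The inconsistency is real and explicit: protocol 4.29 assigns an analysis to the SAP, and the SAP's own scope sentence rules it out. It affects two secondary outcomes, not the primary test. Under the assumed inputs the full-follow-up rate ratio moves towards 1 by about 0.02 to 0.12 (arithmetic) or 0.03 to 0.11 (simulation). These sizes depend on escalation frequencies, timing and effects that the documents do not give; the omission does not.

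A reader might infer more than the documents support:

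- That the bias goes wholly unexamined. It does not, given the by-arm escalation comparison.
- That a null rate ratio could not be told apart from dilution. In these illustrations a true 0.65 reaches at most 0.77, which is not null, and the censored analysis would inform the question without settling it.
- That the analysis was deleted at SAP version 2.0. The change log for 9.10 records only the removed per-protocol analysis, and version 1.0 is not available, so its silence shows nothing either way.
- That SAP 9.2 is a second contradiction. Its checks on skewness and outliers sit awkwardly beside the scope sentence in 9.10 but have nothing to do with escalation.

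**What to change.** In SAP 9.10, change the scope sentence and add a paragraph along these lines: for the rate of URTI-related relapse and the rate of any relapse, the Poisson model of 9.6 will be repeated with the relapse count and the time offset both truncated at first escalation. The result will be shown beside the full 12-month estimate and labelled supportive, because censoring at escalation is informative.

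Two details must be settled first.

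- **Date of escalation.** SAP 9.4 derives most escalations by comparing successive visits. Use the recorded start date of the added agent; where there is none, use the visit at which the category change first appears. Visits are three months apart, so the second rule can date an escalation late.
- **Definition of escalation.** SAP 9.4 counts a move from no background therapy to maintenance prednisolone alone, while protocol 4.10 speaks of adding a new immunosuppressive agent. The two must be reconciled and the definition used for censoring stated.

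The cost is a short SAP amendment, one derived date per child and two further model fits; sample size and alpha are unchanged. The downside is that the censored estimate has its own bias and cannot replace the main analysis. If the sponsor prefers not to run it, the omission should be justified in the SAP and protocol 4.29 amended, which leaves the question open. Either step should precede the final analysis, since SAP 5.6 says the trial statistician has been unblinded for the interim analyses.
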